## Methods

### Study design

The present study follows a hybrid type 1 study design [19], focusing on implementation process factors and outcomes in the context of an effectiveness trial in a prospective quasi-experimental study with control group. A mixed-methods process evaluation among healthcare professionals examines the feasibility and potential barriers and facilitators of ParkinsonAKTIV for routine care, as well as the communication within the regional multidisciplinary Parkinson’s Network Muensterland (PNM+) consisting of medical and non-medical professionals involved in the treatment of patients with PD. For this purpose, quantitative results from a social network analysis and a survey among healthcare professionals will be triangulated with data from qualitative stakeholder interviews and focus group discussions.

Further, the quantitative effectiveness evaluation with two study arms (i.e., intervention arm and observational control arm) examines PD patient’s health-related quality of life and physician-assessed PD patient’s health status (e.g., with the Unified Parkinson Disease Rating Scale (UPDRS)). Moreover, a health economic evaluation of the ParkinsonAKTIV intervention is conducted using patient-reported outcomes and routine data from a German statutory health insurance.

The study observation period is set to 12 months, and data for the effectiveness evaluation and the associated health economic evaluation will be collected at five timepoints, as shown in Table 1.

**Table 1 Tab1:** Trial flow-chart according to SPIRIT guidelines with schedule of enrollment, intervention, and assessment

Timepoint	Study period					
	Preceding study	Enrolment/allocation	Post-allocation			Close-out
	− *t*_1 (12 months prior)_	0	*t*_1_	*t*_2_	*t*_3_	*t*_4 (12 months)_
*Enrolment*						
Eligibility screen		X				
Informed consent		X				
Allocation		X				
*Interventions*						
ParkinsonAKTIV						
Control Group (treatment as usual)						
*Assessments*						
Demographic aspects		X				
PDQ-39		X		X^a^		X
FIMA		X		X^a^		X
Schwab & England—activities of daily living scale		X^a^	X^a^	X^a^	X^a^	X^a^
UPDRS		X^a^	X^a^	X^a^	X^a^	X^a^
Hoehn & Yahr scale		X^a^	X^a^	X^a^	X^a^	X^a^
Routine data	X	X	X	X	X	X

PDQ-39 Assessment of patient-reported health-related quality of life with the Parkinson’s Disease Questionnaire. *FIMA* assessment of patient-reported healthcare costs. *UPDRS* assessment of patient’s PD-related status through neurologists

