^a^Only assessed in the intervention group

This study is registered at ClinicalTrials.gov (registration number NCT05251298). Ethical approval has been given by the ethics committee of the Medical Association Westphalia-Lippe and the University of Muenster (approval number: 2021-356-f-S).

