### Effectiveness evaluation

*Recruitment of intervention group* Recruitment of PwP takes place during face-to-face consultations by their treating neurologists where further information about ParkinsonAKTIV is provided. Until the caseload is reached, all new patients that fulfil the inclusion criteria, will be enrolled into the intervention arm. Additional information about the procedure for participation is available on the PNM+ website as well as flyers.

*Recruitment of control group* To compare the treatment of PwP in ParkinsonAKTIV with standard care, members of a nationwide support group for PD, the Deutsche Parkinson Vereinigung e. V. (dPV), are approached for study participation through their member’s journal. The dPV member pool will be approached twice for participation in the survey, once for the baseline survey and once at the end of the study.

Patients eligible for the intervention arm must fulfill the following inclusion and exclusion criteria:

*Inclusion criteria*
Primary PD according to the international classification (ICD 10 G20.x)Age of ≥ 30 yearsExisting medical treatmentPD care must be fully provided in the region Muensterland, Tecklenburger Land and the district and city of Osnabrueck

*Exclusion criteria*
Secondary PDInsufficient knowledge of the German languageIntellectually and linguistically unable to answer the questionnaires

*Data collection* For the effectiveness evaluation and the health economic evaluation, quantitative data will be collected via paper–pencil surveys among PD patients (i.e., primary outcome: health-related quality of life and secondary outcomes: patient-reported healthcare costs, see Table 1). In addition, neurologists assess disease specific measures during their face-to-face consultations (i.e., secondary outcomes: disease severity and PD symptom severity, see Table 1).

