*Sample size calculation* The sample size calculation is based on the primary outcome, quality of life. According to a-priori power calculation, based on an independent t-test and an effect size of d = 0.3 [3, 11]. With an alpha of 0.05 and a two-tailed comparison of means, a sample size of 176 PwP for each group would be sufficient to achieve a power of 0.80. In total, a case number of 352 PwP is needed due to the 1:1 matching. Considering a loss to follow-up in the intervention arm (estimated at 5%) [2], a total of 185 PwP needs to be initially included. PwP in the control groups will be surveyed via dPV. One study has been identified that recruited PwP via dPV with a resulting response rate of approximately 11% [12]. Considering a similar response rate of 11% for the ParkinsonAKTIV study and dPV’s current approximately 19,000 members across Germany, the inclusion of 185 PwP in the control arm appears to be reachable.

*Primary outcome* The primary outcome is health-related quality of life, assessed using the Parkinson’s Disease Questionnaire (PDQ-39, [1]). The PDQ-39 consists of 39 questions, subdivided into eight dimensions including items on symptoms, opportunities to participate, mobility and interferences in activities of daily living. Each question can be answered with following categories: “never” (= 0 points), “rarely” (= 1 point),” sometimes” (= 2 points), “often” (= 3 points) and “always” (= 4 points). A higher score indicates a reduction in quality of life (PDQ-39, [1]).

*Secondary outcomes. * The severity of PD symptoms will be assessed using the UPDRS, which evaluates various aspects of PD [5]. This instrument includes four different categories containing Part I: Non-Motor Aspects of Experiences of Daily Living, Part II: Motor Aspects of Experiences of Daily Living, Part III: Motor Examination and Part IV: Motor Complications. The questionnaire will be conducted during an interview with the respective patient by the treating neurologist. The UPDRS total score ranges from 0 to 199 points. A higher score indicates a physical or cognitive impairment of PwP [5].

The symptom progression of PD will be assessed by the treating neurologist using the Hoehn and Yahr scale [7], which comprises eight different disease stages. A higher disease stage indicates a higher limitation due to the PD [9].

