The severity of PD and activities of daily living will be assessed using the PD-specific Schwab and England Activities of Daily Living scale [14] by the treating neurologist. This scale rates the functional status of patients with PD on a scale from 0, indicating worst possible function, to 100, indicating no impairment.

Healthcare service utilization will be measured using the generic Questionnaire for Health-Related Resource Use in an Elderly Population (FIMA) [15]. It contains 28 questions that consider the patients’ utilization and healthcare costs of outpatient and inpatient treatments, medications, and other treatment procedures, such as physical therapy.

*Health economic evaluation* The health economic evaluation will be performed as a cost-effectiveness analysis considering total costs (direct and indirect costs) collected from patients via FIMA and quality of life as effect measures collected via PDQ-39. In addition, a cost analysis from a payer’s perspective will be performed using routine data from a statutory health insurance.

*Data analysis* Descriptive and associated analyses will be conducted to determine sample characteristics and provide summaries of outcome measures.

The primary and secondary outcomes will be evaluated according to the intention-to-treat principle. To test the robustness of the data, per-protocol analysis with complete cases only will be performed.

For the analysis of the primary outcome measure, PD-specific quality of life, all 39 items will be grouped into eight index scores, which then represent a percentage value between 0 and 100 (100 = many health problems). In a next step, linear models will be used to examine the difference in primary outcome between groups and will be reported as gain in quality of life within the 12-monthts observation period, with a 95% confidence interval. Sensitivity analyses will be conducted using multiple regression analysis, considering covariates such as age, gender, or duration of PD.

Secondary outcomes will be analyzed with dependent t-tests, to compare for potential differences in the intervention group within the course of the study (12 months).

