## Perspective

To the best of our knowledge, this is the first study testing and evaluating the implementation of a multidisciplinary treatment coordination platform for PwP in Germany. The ParkinsonAKTIV study aims to test a multidisciplinary, digitalized approach called JamesAKTIV, including a wide range of healthcare professionals intimately involved in the community-based care for PwP. It is anticipated that ParkinsonAKTIV can overcome current barriers to communication and coordination within PwPs’ care paths with special regard to non-pharmacological therapies. The German PD care landscape is characterized by a fragmented system with different healthcare professionals caring for PwP, hence prescribing PD treatment to patients yet not communicating with each other about the respective patient. The multidisciplinary communication and coordination platform JamesAKTIV is designed to address communication barriers by using digitalized quickcards as means of communication about PwPs' treatment.

An outstanding strength of ParkinsonAKTIV is its study design. Combining quantitative and qualitative data collection through a process evaluation and an effectiveness evaluation, gaining deeper insights into patient’s quality of life and ParkinsonAKTIV’s cost-effectiveness. Specifically, during process evaluation, a social network analysis will be conducted which is, to our knowledge, a novelty in analyzing teamwork in multidisciplinary PD healthcare teams.

It is assumed that the results of this study will further strengthen ParkinsonAKTIV. First, the findings are expected to provide evidence of an increase in quality of life of PwP, less severe PD symptoms, and a better ability to participate in activities of daily living. Second, ParkinsonAKTIV has high potential of increasing PwPs’ quality of care through sufficient and more tailored prescription of non-pharmacological therapies. Third, improved communication among health professionals could lead to an increased patient safety.

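### UPDRS is presented as an outcome of the two-arm evaluation, but it and the other clinician-rated scales have no control data and are tested only before-after; the same rule, read literally, leaves FIMA utilisation without a between-arm comparison

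*Protocol article*

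**What the plan says.** The Study design section says that "the quantitative effectiveness evaluation with two study arms (i.e., intervention arm and observational control arm) examines" quality of life and physician-assessed health status, with the UPDRS given as the example. The Methods part of the Abstract does the same: it names the UPDRS under a quasi-experimental approach with a control group.

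In Table 1, every UPDRS, Hoehn and Yahr, and Schwab and England entry, from baseline to 12 months, carries the footnote "Only assessed in the intervention group". The PDQ-39 and FIMA are collected at baseline and 12 months in both arms, with one further assessment (t2) in the intervention arm.

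The Data analysis paragraph of the Effectiveness evaluation gives one rule: "Secondary outcomes will be analyzed with dependent t-tests, to compare for potential differences in the intervention group" over the 12 months. FIMA falls under this rule, because the Data collection paragraph lists "secondary outcomes: patient-reported healthcare costs" beside the clinician-rated scales. Separately, the health economic paragraphs take total costs from FIMA and compare mean total costs between the arms in an ICER, with 5,000 bootstrap replications, cost-effectiveness planes and an acceptability curve.

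The Perspective section says "the findings are expected to provide evidence of an increase in quality of life of PwP, less severe PD symptoms", followed by better ability in daily activities. The Abstract repeats this.

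**The concern.** The article attributes to the UPDRS a property that the schedule of assessments does not give it. A reader of the Abstract or Study design section would take any reported change in UPDRS as a contrast with standard care. No such contrast can be formed, because no control value is collected. The same holds for Hoehn and Yahr and for Schwab and England.

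The paired test answers whether the mean score changed in treated patients. It does not say why. The Introduction calls the disease generally slowly progressive, so some change is expected without any intervention effect. The scales are rated by the treating neurologist, who also enrols the patient and documents treatment on the platform, so the rater knows the allocation. Regression to the mean is a third explanation. If the expectation in the Perspective section is carried into the report, an uncontrolled p-value may be read as effectiveness on symptoms.

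FIMA has the opposite problem. Control data exist, but the secondary-outcome rule does not use them for utilisation. The article expects more sufficient and better tailored prescription of non-pharmacological therapy. Therapy use recorded in FIMA bears directly on that, and a single total-cost contrast in the ICER cannot show it.

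**Working it through.** **1. The plan's own figure.** The sample size calculation is "based on an independent t-test and an effect size of d = 0.3". It uses a two-sided alpha of 0.05 and power of 0.80, and arrives at 176 patients per group.

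- Normal approximation: n = 2(1.960 + 0.842)² / 0.3² = 174.4, rounded up to 175 per group.
- Noncentral t: 175.38, rounded up to 176 per group. With 176, power is 0.80.

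The stated 176 reproduces. It covers the between-group test of the PDQ-39 only; no calculation is given for the secondary outcomes.

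**2. Which comparisons the schedule allows.**

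| Outcome | Intervention arm | Control arm | Stated analysis |
|---|---|---|---|
| PDQ-39 | baseline, t2, 12 months | baseline, 12 months | between arms |
| UPDRS, Hoehn and Yahr, Schwab and England | all five timepoints | none | paired t-tests, intervention arm |
| FIMA total cost | baseline, t2, 12 months | baseline, 12 months | between arms, in the ICER |
| FIMA utilisation | baseline, t2, 12 months | baseline, 12 months | paired t-tests, intervention arm, by the general rule |

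For the second row the gap lies in data collection, so a different test cannot close it. For the fourth row it lies in the analysis rule alone.

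**3. How the paired test behaves when scores shift for other reasons.** The documents give no SD, within-patient correlation or natural course for these scales, so the shifts below are assumptions. Inputs: n = 176 pairs (the plan's group size, taken as completers), two-sided alpha 0.05 (stated for the primary outcome and assumed here), and dz = mean change divided by the SD of the differences. The noncentrality parameter is dz × √176 = dz × 13.27, with 175 degrees of freedom and a critical value of about 1.974.

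| dz with no intervention effect | Noncentrality | Probability of p < 0.05 |
|---|---|---|
| 0 | 0 | 0.05 |
| 0.1 | 1.33 | 0.26 |
| 0.2 | 2.65 | 0.75 |
| 0.3 | 3.98 | 0.98 |

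The shift that gives 80% probability is dz = 0.212; as a check, (1.974 + 0.842) / 13.27 = 0.212.

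The table holds for either direction. A shift towards improvement would look like benefit. A shift towards worsening would look like harm, or would cancel a benefit: a true gain of 0.2 with progression of 0.2 leaves dz = 0, and the test then rejects with probability 0.05.

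**The case against.** The best defence is that nothing is concealed. The Table 1 footnote and the analysis sentence both confine these scales to the intervention group, and the Perspective section concedes that the study is not a classical randomised trial. No passage says that within-arm p-values will be read against control. The null hypothesis of the paired test is no change, so rejecting it when scores have truly moved is not a test error, and natural progression would tend to work against showing improvement. All of this is correct. It makes the problem one of interpretation and wording. It does not remove the contradiction: the conceded limitation concerns randomisation, and the article nowhere says outright that the UPDRS lacks the control group under which it is presented.

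A reader might infer more than the document supports:

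- That FIMA is never compared between arms. It is: FIMA total costs enter the ICER with bootstrap uncertainty. Only utilisation is left to the within-arm rule.
- That the t-tests breach intention-to-treat by dropping patients without a 12-month value, or use only two of five visits. The article applies intention-to-treat to secondary outcomes, reserves complete cases for the per-protocol check, and names no visit pair. Missing-data handling may be set out in the analysis plan.
- That the expected gain in daily-living ability has no controlled basis. The PDQ-39 contains items on daily activities and participation and is measured in both arms.
- That a mixed or ordinal model would repair the clinician-rated scales. It would describe their course better, but would supply no control.

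**Conclusion.** The point holds in two parts. First, the article presents the UPDRS as part of a two-arm evaluation and expects evidence of less severe symptoms, while its own schedule and analysis rule permit only uncontrolled before-after change for all three clinician-rated scales. Evidence of an intervention effect on symptom severity cannot come from them. Second, FIMA utilisation has control data at baseline and 12 months, but the stated rule does not use them.

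The rejection probabilities of 0.26, 0.75 and 0.98 are illustrative. They rest on assumed shifts, 176 complete pairs and alpha of 0.05, and are not forecasts for this trial. The contradiction does not depend on them. The primary outcome, the sample size and the cost-effectiveness analysis are unaffected, and no stated figure is shown to be wrong.

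**What to change.** 1. In the Abstract and the Study design section, state that the UPDRS, Hoehn and Yahr, and Schwab and England scales are assessed without a control arm. In the Data analysis paragraph, report them as uncontrolled, descriptive change with confidence intervals, preferably using all five scheduled assessments. In the Abstract and Perspective, do not claim evidence of an intervention effect on symptom severity from these scales, and rest any daily-living claim on the controlled PDQ-39.
2. Exempt FIMA from the within-arm rule. Compare utilisation, including physical and other therapy use, between arms at 12 months, adjusting for the baseline value and for the covariates already listed for the sensitivity analyses, such as age, gender and duration of disease. The article places that adjustment in the sensitivity analyses and not in the primary model, so it must be specified for FIMA. Baseline adjustment also assumes that each control participant's two questionnaires can be linked. The article says only that the support-group membership is approached twice, so this should be confirmed.

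The cost is a weaker stated claim for the clinician-rated scales and a little more analysis. No new data are needed.

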## Introduction

Parkinson’s disease (PD) is the second most common neurodegenerative disorder. Its course is generally slowly progressive and results in a variety of motor and non-motor symptoms [18]. In 2019, worldwide, approximately 8.5 million people have been affected by PD [16, 18]. Patients with PD (PwP) require a comprehensive and individualized management including medications, deep brain stimulation, and non-pharmacological treatments, such as physical therapy, occupational therapy as well as speech and swallowing therapy [4]. International network approaches have been shown to improve quality of life, reduce hospital admissions, and minimize the general burden of disease for PwP and their caregivers [11]. Notably, a study based on German routine data from a statutory health insurance revealed that there is a nationwide lack in non-pharmacological therapies for PwP [6]. Due to the fragmented German healthcare system with its inadequate collaboration and communication between healthcare professionals, an unmet need for comprehensive PD treatment approaches exists. Hence, an innovative treatment approach is needed to address and bridge these gaps in communication and collaboration through including a wide range of healthcare professionals, intimately involved in a community-care setting.

The *ParkinsonAKTIV* study, described in this paper, implements and evaluates such an innovative, multidisciplinary and comprehensive treatment approach for PwP in a region in northwestern Germany. As an essential part of the ParkinsonAKTIV study, an online communication platform to enhance PD healthcare professionals’ communication, called *JamesAKTIV*, is built and evaluated. The ParkinsonAKTIV study is set out to reach two aims: (1) first, to understand the implementation process and care process of ParkinsonAKTIV (and JamesAKTIV) through a detailed *process evaluation*. (2) Second, to gather evidence on the impact on patient-related outcomes, such as health-related quality of life and healthcare costs for PwP, through an *effectiveness evaluation*.

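### UPDRS, Hoehn & Yahr and Schwab & England are measured and tested in the intervention arm only, so their before–after tests cannot attribute change to ParkinsonAKTIV and can miss a real slowing of progression

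*Protocol article*

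**What the plan says.** **Measurement.** In Table 1 (Methods, Study design) the three clinician-rated scales carry footnote a at all five timepoints. The footnote reads "Only assessed in the intervention group". Control patients are recruited through a patient association's journal and answer a survey.

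**Test.** Effectiveness evaluation, Data analysis: "Secondary outcomes will be analyzed with dependent t-tests, to compare for potential differences in the intervention group within the course of the study". The period is 12 months.

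**Rater.** Under Secondary outcomes, on the UPDRS: "The questionnaire will be conducted during an interview with the respective patient by the treating neurologist". The treating neurologist also rates the other two scales. Under Use of JamesAKTIV, the same neurologist opens the patient's case and documents treatment on the platform.

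**How the design is presented.** Study design says that "the quantitative effectiveness evaluation with two study arms (i.e., intervention arm and observational control arm") examines both quality of life and physician-assessed health status, with the UPDRS as the example. The Methods part of the abstract does likewise.

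**What is expected.** The abstract and the Perspective section expect the findings to give evidence of "less severe PD symptoms, and a better ability to participate in activities of daily living".

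**Natural course.** The Introduction says of Parkinson's disease: "Its course is generally slowly progressive".

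**The concern.** A dependent t-test has zero mean change as its null. By the article's own description of the disease, zero is not what should be expected without benefit; some worsening is. Two readings then go wrong.

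- **Benefit read as failure.** If ParkinsonAKTIV slows worsening without reversing it, the arm shows no change or a net decline.
- **Improvement read as effect.** If scores improve, other treatment changes during the year, or unblinded rating by a neurologist who takes part in the intervention, are alternative explanations. A single arm cannot separate these from the intervention.

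At stake is the conclusion on clinician-rated symptoms and function. These three are the only clinician-rated outcomes in the trial. A reader of the abstract or Study design would think they are compared with a control group.

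**Working it through.** **1. The plan's own figure.** Sample size calculation: d = 0.3, two-sided alpha 0.05, power 0.80, independent t-test. The normal approximation gives n = 2 × (1.960 + 0.842)² / 0.3² = 174.4, so 175 per group. The exact t-test gives 175.4, so 176, with power 0.801. The stated 176 reproduces. With 5% loss, 176 / 0.95 = 185.3, consistent with the stated 185 apart from rounding. I use n = 176 below.

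**2. What the paired test responds to.** Let w be natural worsening over 12 months and s the true slowing due to ParkinsonAKTIV, both in SDs of the 12-month change. Sign each scale so that positive is worse (Schwab & England runs the other way). The mean change in the arm is w − s. The noncentrality of the paired t-test is (w − s) × √176 = 13.27 × (w − s), with 175 degrees of freedom. The test depends on the difference, not on s.

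The article gives neither a progression rate nor an SD of change, so w and s are assumptions shown over a range.

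**3. No intervention effect, net drift from other causes (either direction).**

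| Net drift (SD) | Noncentrality | P(p<0.05) |
|---|---|---|
| 0.1 | 1.33 | 26% |
| 0.2 | 2.65 | 75% |
| 0.3 | 3.98 | 98% |

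**4. Real slowing.** I set s = 0.3, borrowing the plan's d for the primary outcome, and vary w. The last column is a hypothetical independent t-test on change with 176 per arm and an unbiased control.

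| w | w − s | P(significant worsening) | P(significant improvement) | Two-arm power |
|---|---|---|---|---|
| 0 | −0.3 | <0.1% | 97.7% | 80.1% |
| 0.1 | −0.2 | <0.1% | 75.1% | 80.1% |
| 0.2 | −0.1 | 0.1% | 26.1% | 80.1% |
| 0.3 | 0 | 2.5% | 2.5% | 80.1% |
| 0.4 | +0.1 | 26.1% | 0.1% | 80.1% |
| 0.5 | +0.2 | 75.1% | <0.1% | 80.1% |

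The same true benefit gives anything from near-certain improvement to probable significant worsening, depending only on how fast patients would have declined. When w = s, rejection is 5% in total whatever the size of s.

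**5. Scope.** The PDQ-39 is collected in both arms at baseline and 12 months and compared between groups. FIMA is also collected in both arms and feeds a between-arm cost-effectiveness ratio. The problem is confined to the three clinician-rated scales.

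**The case against.** The strongest case against the point runs as follows.

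- **The single-arm status is disclosed.** Table 1, its footnote and the Data analysis sentence all say so, and nowhere is the paired test called an estimate of a between-arm effect. That stands. It does not cure the abstract and Study design, which read as if the UPDRS were compared with a control. The limitations paragraph in Perspective concedes only that the study is not a classical RCT.
- **The outcomes are secondary.** This stands, and it keeps the point below a must-fix.
- **An analysis plan or full protocol may say more.** It could relabel the analysis, but the footnote leaves no control data on these scales from which to form a comparison.

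A reader might also infer stronger things that the document does not support.

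- *That the plan promises a symptom benefit.* It says expected, and no decision rule ties a significant paired test to that conclusion.
- *That the test cannot show milder symptoms at all.* It can show a within-patient fall in scores; what it cannot do is attribute the fall.
- *That the percentages in step 3 are an inflated type I error.* The null tested, zero mean change, is false in those scenarios. The error lies in reading rejection as an intervention effect.
- *That regression to the mean, or any rival cause, explains an improvement equally well.* No inclusion criterion selects on these scores, and nothing in the article sizes the rival causes. Indeed, where the natural course is worsening, a zero-change null is conservative against improvement.

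**Conclusion.** The point holds as a should-fix on interpretation. The three clinician-rated scales have no comparator, and the planned test mixes natural progression with any effect of ParkinsonAKTIV. It can document change but not attribute it, and it can miss real slowing.

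That conclusion rests only on the arm-restricted measurement, the paired test and the article's statement that the disease progresses. The sizes do rest on assumptions: n = 176, drifts of 0.1 to 0.3 SD for the 26%, 75% and 98%, and s = 0.3 SD with progression of 0 to 0.5 SD for the slowing table. They are illustrations, not forecasts. The primary PDQ-39 comparison, the sample size and the cost-effectiveness analysis are not touched by this point.

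**What to change.** 1. **Abstract (Methods) and Study design:** state that UPDRS, Hoehn & Yahr and Schwab & England are assessed in the intervention arm only and are not part of the controlled comparison.
2. **Data analysis:** for these scales, report mean 12-month change with 95% CI, labelled descriptive within-arm change and not a test of effect.
3. **Abstract (Perspective) and Perspective section:** drop the expectation that these scales will give evidence of an intervention effect. Base any claim on symptoms, mobility or daily living on the between-arm comparison of the relevant PDQ-39 dimensions, using the planned linear model and labelled secondary or exploratory.

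Cost: wording changes and a further use of a model already planned. No new data are needed, since the PDQ-39 is collected in both arms at baseline and 12 months and is already to be scored into eight indices. The downside is a weaker claim from the clinician-rated scales and a few extra comparisons. Those comparisons remain non-randomised, so the exploratory label matters.

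### FIMA service use is collected in both arms at baseline and 12 months, but the only secondary-outcome test is within the intervention arm, so no between-arm estimate of service or therapy use is planned

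*Protocol article*

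**What the plan says.** All places are in the protocol article, mostly under Effectiveness evaluation.

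- **Status of FIMA.** Data collection lists, among the patient surveys, "secondary outcomes: patient-reported healthcare costs". The Secondary outcomes text presents FIMA as the measure of service utilisation, covering "outpatient and inpatient treatments, medications, and other treatment procedures, such as physical therapy".
- **Schedule.** In Table 1, FIMA at baseline and at t4 (12 months) carries no footnote, so both arms complete it. Only t2 is marked as intervention group only. UPDRS, Hoehn & Yahr and Schwab & England carry that footnote at every visit.
- **Stated test.** Under Data analysis: "Secondary outcomes will be analyzed with dependent t-tests", with the purpose "to compare for potential differences in the intervention group within the course of the study". A between-group linear model is stated for the primary outcome only.
- **Other use of FIMA.** The Health economic evaluation builds total costs from FIMA and contrasts the arms in an ICER, with 5,000 bootstrap replications, cost-effectiveness planes and an acceptability curve.
- **Why therapy use matters here.** The Introduction motivates the study by a finding that "there is a nationwide lack in non-pharmacological therapies for PwP". The Perspective section expects the programme to raise "quality of care through sufficient and more tailored prescription of non-pharmacological therapies".

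**The concern.** For the three neurologist-rated scales a one-arm test is all the design allows, because the control arm never has them. FIMA is the one secondary instrument with control data at both ends of follow-up, and the general rule for secondary outcomes covers it as well. Followed as written, that rule tests whether service use changed among intervention patients. It does not test whether it changed by more than under usual care.

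Service use can move over a year for reasons unrelated to the programme, such as disease progression or a shift in the availability of services. A paired test attributes all of it to ParkinsonAKTIV.

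Interpretation of the primary result suffers too. Provision of non-pharmacological therapy is what the programme is meant to change. If PDQ-39 shows no difference, readers will ask whether therapy failed to rise or rose without benefit. The stated analyses give no between-arm answer.

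**Working it through.** **1. The plan's own figure.** Inputs from Sample size calculation: d = 0.3, two-sided alpha 0.05, power 0.80, independent t-test. The normal approximation gives 175 per group. The noncentral t solution is 175.4, rounded up to 176, and power at 176 per group is 0.801. The stated 176 is reproduced.

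**2. Which secondary instruments have control data (Table 1).**

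| Instrument | Control arm, baseline | Control arm, 12 months | One-arm test unavoidable? |
|---|---|---|---|
| UPDRS | no | no | yes |
| Hoehn & Yahr | no | no | yes |
| Schwab & England | no | no | yes |
| FIMA | yes | yes | no |

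**3. What the paired test does under a common drift.** Suppose mean service use shifts by δ (in between-person SD units) in both arms and the intervention has no effect. With equal SDs and baseline to 12-month correlation r, the SD of change is √(2(1 − r)). The standardised change is dz = δ / √(2(1 − r)), and the noncentrality is dz × √176. For δ = 0.1 and r = 0.5, dz = 0.1 and the noncentrality is 0.1 × 13.27 = 1.33, which gives a rejection rate of 26%. The article gives neither δ nor r, so both are assumed and shown as a range:

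| Common drift δ | r = 0.3 | r = 0.5 | r = 0.7 |
|---|---|---|---|
| 0.05 SD | 8.6% | 10.1% | 13.6% |
| 0.1 SD | 20.0% | 26.1% | 39.9% |
| 0.2 SD | 60.6% | 75.1% | 92.6% |

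The nominal rate is 5%.

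**4. What the planned sample offers between arms.** With 176 per arm, 80% power and two-sided 0.05, the detectable difference is 0.299 SD. Baseline adjustment multiplies this by √(1 − r²):

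- r = 0.3: 0.299 × 0.954 = 0.29 SD
- r = 0.5: 0.299 × 0.866 = 0.26 SD
- r = 0.7: 0.299 × 0.714 = 0.21 SD

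**5. A caution on scales.** The paired test on 176 patients has 80% power at dz = 0.212, but that is in SDs of change. In between-person SDs it is 0.212 × √(2(1 − r)), that is 0.25, 0.21 and 0.16 for r = 0.3, 0.5 and 0.7. It should not be set directly beside the figures in step 4.

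All of these are t-test approximations. Service use is likely to be skewed, so they indicate scale and are not a power calculation for FIMA.

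**The case against.** The strongest reply is that the dependent t-test sentence was written with the neurologist-rated scales in mind. It speaks of the intervention group, and those scales exist only there. FIMA has its own economic section, where costs, the patient-reported secondary outcome named under Data collection, are compared between arms with bootstrap uncertainty. The intent may well be so, but the sentence covers secondary outcomes without exception, and the economic section compares total costs, not service use.

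Several stronger readings that a reader might infer do not stand:

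- *That control FIMA data are thrown away.* They supply the control-arm cost in the ICER.
- *That therapy use is a declared endpoint tested in the wrong way.* It is not named as an outcome. It is one part of what FIMA records, and the prescription claims in Perspective are expectations, not hypotheses.
- *That therapy cost could never be separated from hospital or drug cost.* FIMA records these separately, descriptive summaries are promised, and a condensed article's silence on components is not a prohibition.

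The payer-perspective analysis of routine insurance data does not close the gap. It is described as a cost analysis, and the article does not say that it includes controls or estimates therapy use.

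The limits of the comparison also stand. Controls are members of a nationwide support group and intervention patients come from one region, so access to therapy may differ for reasons other than the programme. The control pool is approached twice, and the article does not say that the two responses are linked by person.

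**Conclusion.** The point holds in limited form. FIMA is a secondary outcome with data from both arms at baseline and 12 months, and the only test stated for secondary outcomes uses one arm. Control FIMA data serve only as total costs in the ICER, so no between-arm estimate of service or therapy use is planned. This is a stated rule that does not suit one of the outcomes it covers, not a detail left to a fuller document.

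The consequence depends on drift that the article does not quantify. Under an assumed common drift of 0.1 to 0.2 SD and correlations of 0.3 to 0.7, the one-arm test would find a change in 20% to 93% of trials in which the programme adds nothing. If there is no drift, the rate stays at 5%.

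A reader might infer that a between-arm analysis would give a clean causal estimate. It would not: it removes only the drift that the two arms share and leaves confounding between two differently recruited groups. It is still more informative than a before-after change alone. The primary outcome is untouched. The change should be made, but it does not decide the trial's main conclusion.

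**What to change.** Amend the Data analysis paragraph as follows:

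1. Limit the dependent t-test rule to UPDRS, Hoehn & Yahr and Schwab & England.
2. Analyse FIMA service use between arms at 12 months, with non-pharmacological therapy as a named component, using only the occasions common to both arms (baseline and t4).
3. Adjust for the baseline FIMA value and for the matching or covariates of the primary model.
4. Use a method suited to skewed data, such as a count model or bootstrap intervals.
5. Keep the within-arm change, including t2, as description.
6. State that the between-arm estimate is non-randomised and whether control responses are linked across the two surveys. Baseline adjustment depends on that link.

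The cost is one paragraph of wording and a few more model runs, with no extra patients, visits or questionnaires. If the two control surveys cannot be linked, individual baseline adjustment for controls is not possible and the comparison is weaker. That should be settled before the analysis is fixed.
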